At 15 days after hospital discharge after intestinal or urinary ostomy placement (baseline), the stomatherapists, in the six centres participating in the study, will identify possible candidates, propose the study to them, inform them, and ask them to sign the informed consent. They will then screen the patients, according to inclusion / exclusion criteria. Patients who pass the screening will be evaluated for sociodemographic (e.g. age, sex) and clinical characteristics (type of ostomy packing and comorbidities, using the Charlson Comorbidity Index ^27^). Patients who do not pass the screening will not be enroled in the study and will be cared for according to common clinical practice.

Patients will also be interviewed using validated instruments (questionnaires and psychometric scales) investigating self-care behaviours, quality of life, depression, adaptation, stomal and peristomal complications, number of inappropriate accesses to health services, lost working days, and mobility (Table 2 and appendices). These same variables will subsequently be reevaluated in both the experimental and control arms at 1, 3 and 6 months after the end of the intervention.

The data collection process will be carried out by specially trained research nurse assistants, who will not know the randomisation arm to which patients have been assigned.

*Randomization and blinding*

After enrolment (at 15 days after discharge) and data collection at baseline, patients will be assigned to the two planned study arms by randomisation stratified by type and sex of ostomy. Randomisation will be implemented in blocks of 6 patients to ensure the same number of individuals per arm. Randomisation blocks will be created until the predetermined sample size is reached. Then, again causally, the blocks will be randomly allocated to enrolment centres.

The stomatherapist who will perform the educational intervention will know the allocation of patients to the two groups, but will not participate in data collection and analysis. Therefore, in this study, the researchers and research assistants who will collect endpoint data will be blinded, and this will also apply to those who will perform data collection and analysis.

*Measurement of outcomes*

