
*Statistical analysis*

Sample size. The sample size of the present study was calculated with Sampsize.31 Assuming a power of 80% and an alpha error of 2.5%, for a standardised non-inferiority margin equivalent to 0.25, a sample size of 366 subjects (183 for each arm) will be needed to demonstrate non-inferiority of the intervention by remote versus standardised means, relative to the primary outcome (self-care maintenance). Estimating a possible dropout of 10% at 1 month after the end of the educational intervention, it will be necessary to enrol 384 subjects (192 for each arm). Considering that there will be six centres participating in the study, each centre will enrol 64 patients (32 per arm).

Non-inferiority margins. The non-inferiority margin established for the primary outcome (self-care maintenance) will be four points. This margin corresponds to half of the minimum score considered clinically significant (equivalent to 0.5 standard deviations) on the standardized scales of self-care^32^. The choice of this margin of inferiority arose after careful clinical judgment of the research team and based on the general recommendation to adopt a value that is smaller than the minimum clinically significant score and is, at the same time, clinically irrelevant ^33^.

For secondary outcomes self-care monitoring, self-care management and self-efficacy, the same margin of non-inferiority is established, a difference of 8 points being valid in these scales as the minimum clinically significant score ^32^.

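### Enrolling 384 to keep 366 evaluable allows for 4.7% dropout, not the stated 10%; at 10% only about 346 (173 per arm) remain

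*Protocol*

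**What the plan says.** All the figures stand in the sample size paragraph of the Protocol (METHODS, Statistical analysis). The evaluable requirement is given as "a sample size of 366 subjects (183 for each arm) will be needed to demonstrate non-inferiority", based on "Assuming a power of 80% and an alpha error of 2.5"% and "for a standardised non-inferiority margin equivalent to 0.25". The allowance for losses follows: "Estimating a possible dropout of 10% at 1 month after the end of the educational intervention, it will be necessary to enrol 384 subjects", that is 192 per arm. That total is then divided among six sites, so that "each centre will enrol 64 patients (32 per arm").

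The dropout is placed 1 month after the end of the intervention. Under Measurement of outcomes, this is the time point of the primary outcome, self-care maintenance. The protocol gives no other dropout rate.

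**The concern.** Three numbers in one paragraph (366 evaluable, 10% lost, 384 enrolled) cannot all be true. The gap between 384 and 366 is 18 patients, whereas 10% of 384 is about 38. The enrolment target therefore allows for less than half of the loss that the protocol itself expects.

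At stake is the number of patients with a primary outcome. If dropout runs as forecast, the trial falls short of its own evaluable target. The shortfall comes before any per-protocol exclusions. Those matter because the planned analyses accept non-inferiority only if the intention-to-treat and per-protocol analyses both show it, and the sample size makes no further allowance for them. The same figure is passed on to the sites as a recruitment target of 64 each.

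**Working it through.** **Inputs** (Protocol, Sample size paragraph): evaluable N = 366 (183 per arm); dropout d = 10%; enrolled = 384 (192 per arm); six centres; power 80%; alpha 2.5%, read as one-sided to match the lower limit of a 95% confidence interval; margin 0.25 SD. Equal allocation comes from Randomization and blinding. A true difference of zero is my assumption, since none is stated.

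**Trying to reproduce 384 from 366 and 10%**
- Standard formula, N/(1 − d): 366/0.90 = 406.7, so 407. Per arm, 183/0.90 = 203.3, so 204 per arm and 408 in total.
- Common shortcut, N x (1 + d): 366 x 1.10 = 402.6, so 403.
- Neither gives 384. A 5% rate comes close: 366 x 1.05 = 384.3, and 366/0.95 = 385.3. A 5% inflation may have been used, but the document does not say so and the contradiction does not depend on it.

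**What 384 covers**
- Tolerable dropout: 1 − 366/384 = 18/384 = 4.7%.
- Evaluable at 10% dropout: 384 x 0.90 = 345.6, about 346. Per arm: 192 x 0.90 = 172.8, about 173.
- Shortfall: 366 − 346 = 20 patients, or 20/366 = 5.5% of the target.

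**Does rounding to six centres explain it?** No. 6 x 64 = 384, but 408 also divides by six (6 x 68, 34 per arm per centre).

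**Power**, normal approximation, with n per arm: Φ(0.25 x √(n/2) − 1.96)

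| Evaluable per arm | Situation | Power |
|---|---|---|
| 183 | target of 366 met | 0.667 |
| 173 | 384 enrolled, 10% lost | 0.642 |

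The dropout step therefore costs 0.667 − 0.642 = 0.025, about 3 points after rounding (67% to 64%).

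**The rest of the gap to 80% has another cause.** On the stated inputs, n per arm = 2 x ((1.960 + 0.842)/0.25)² = 251.2, so 252 per arm and 504 in total, not 366. If one instead accepts that 183 per arm gives 80%, the effective margin is √(2/183) x (1.960 + 0.842) = 0.293 SD. Power at 173 per arm is then Φ(0.293 x √(173/2) − 1.96), about 78%. On either view the dropout error alone is worth 2 to 3 points.

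**The case against.** The arithmetic is hard to contest; the fair objection concerns weight and remedy.

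- *The effect on power is small.* Quoting 64% against 80% would blame this error for a loss that mostly belongs to the 366. This stands: only 2 to 3 points are due to the dropout step.
- *Moving to 408 would not rescue the trial.* It would add 24 patients and still leave 183 evaluable per arm, with about 67% power on the stated inputs. This stands too. Raising enrolment makes sense only after the 366 has been settled.
- *68 per centre does not fit the randomisation.* Blocks contain 6 patients ("Randomisation will be implemented in blocks of 6 patients to ensure the same number of individuals per arm") and are allocated to centres, so complete blocks give multiples of six per centre. 68 is not one. Nor is the current 64, so this weakness is already in the plan.
- *No per-protocol exclusion rate is given,* so the further loss there cannot be sized. This is true, and no figure is claimed for it.
- *The mixed model might recover the missing patients.* It does not recover those counted here. One month is the first assessment after baseline (Table 2), so a patient lost by then has no follow-up outcome to contribute. The t test that is also planned at each follow-up uses observed outcomes only.

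None of this makes 384 consistent with 366 and 10%.

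**Conclusion.** The enrolment figure is wrong as written. Taking 366 as given, 384 enrolled allows for 4.7% dropout. At the stated 10%, about 346 patients (173 per arm) remain, some 20 below target, and 407 (408 for equal arms) would have to be enrolled to keep 366. These results need only the protocol's own three numbers.

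The power figures (64% at 173 per arm, 67% at 183) also rest on a 0.25 SD margin, one-sided 2.5% and a true difference of zero. About 3 points are due to this error. The failure of 366 to follow from the stated inputs is a separate error that adds to it, and each needs its own correction: mending the 366 alone would leave a faulty inflation step to be applied to the new number.

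**What to change.** Correct the dropout sentence. With enrolment left at 384, it should state that this number allows for 4.7% dropout, that 10% dropout would leave about 346 evaluable (173 per arm), and what the power is at that number. This is a change of wording and adds no patients.

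If the sponsor prefers to keep 366 evaluable at 10% dropout, the enrolment figure becomes 408 (204 per arm; 68 per centre, 34 per arm), which costs 24 more patients. That choice should be made together with a re-derivation of the 366. On the stated inputs the corresponding figures would be 504 evaluable and 504/0.90 = 560 enrolled. Whichever total is chosen, carry it through to the per-centre target, and give that target either as a multiple of the block size of 6 or as approximate.

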2. to evaluate the non-inferiority of an educational intervention carried out remotely (via video call) to persons with intestinal and urinary ostomy on other secondary outcomes such as quality of life, depression, satisfaction with care, adaptation, prevalence of ostomal and peristomal complications, use of health care services, mobility, and number of working days lost, compared to the same intervention carried out in the presence;
3. describe the experience of patients who received the educational intervention performed remotely (via video call) and in presence.

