Planned statistical analyses. Sociodemographic and clinical characteristics, as well as outcome scores, will be described by measures of central tendency (mean or median) and variability (standard deviation or interquartile range), while frequencies and percentages will be used for categorical variables. To investigate differences in sociodemographic and clinical characteristics between randomisation groups, the t test for independent samples and the chi-square test will be used. P values less than 0.05 will be considered statistically significant. To investigate differences in the primary outcome and secondary outcomes of non-inferiority, the student's t test for independent samples will be employed at each follow-up and baseline. A longitudinal linear mixed model will be implemented to analyze the effect of interventions on randomization groups and their interaction with time. This approach, widely used as a substitute for ANOVA (in order to avoid loss of subjects due to missing data), has the advantage of controlling for the phenomenon of "clustering" induced by repeated measures over time for each subject.^34^

Non-inferiority of the experimental intervention remotely compared with the in-presence intervention will be confirmed if the lower extreme of the 95% confidence interval is not below the predetermined non-inferiority margin. Any superiority of the experimental intervention over the active control will be confirmed if the lower end of the 95% confidence interval is simultaneously above the non-inferiority margin and above zero. Given the nature of non-inferiority trials, analyses will be conducted in both intention-to-treat and per-protocol modes, according to CONSORT recommendations.^33^ The hypothesis of non-inferiority will be confirmed only if obtained through both modes of analysis.^35^ For missing data analyses, the distributions of patients lost to follow-up between the two randomisation groups will be compared (using chi-square tests) in order to assess any differences in sociodemographic and/or clinical characteristics, or outcomes. The results obtained will be interpreted in light of any differences found between the groups.

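### The rules for declaring non-inferiority or superiority confirmed are not limited to the primary contrast, so 11 non-primary OSCI contrasts can also be confirmed at a full one-sided 2.5%

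*Protocol*

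**What the plan says.** All references are to the Protocol.

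- **Measurement of outcomes** fixes a single primary contrast: the OSCI self-care maintenance score at 1 month after the educational intervention ends.
- **Sample size** states the error rate once, for that outcome: "Assuming a power of 80% and an alpha error of 2.5%, for a standardised non-inferiority margin equivalent to 0.25".
- **Non-inferiority margins** sets four points for maintenance and then extends it: "For secondary outcomes self-care monitoring, self-care management and self-efficacy, the same margin of non-inferiority is established". No other outcome receives a margin.
- **Introduction.** Objective 1 includes non-inferiority on monitoring and management. Objective 2 goes further: "to evaluate the non-inferiority of an educational intervention carried out remotely (via video call) to persons with intestinal and urinary ostomy on other secondary outcomes".
- **Planned statistical analyses** says: "To investigate differences in the primary outcome and secondary outcomes of non-inferiority, the student's t test for independent samples will be employed at each follow-up". Non-inferiority is then to be confirmed if the lower 95% confidence limit does not fall below the margin. For superiority: "Any superiority of the experimental intervention over the active control will be confirmed if the lower end of the 95% confidence interval is simultaneously above". Its two thresholds are the margin and zero. Non-inferiority must be shown in both the intention-to-treat (ITT) and per-protocol analyses; the text does not state that requirement for superiority.

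Neither rule names the outcome or the visit to which it applies.

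**The concern.** A confirmation rule belongs to the contrast for which the error rate was set. Here the rule is worded for the intervention in general. It follows directly on a sentence that sends primary and secondary non-inferiority outcomes to a test at every follow-up, and three secondary scales carry a formal margin. A reader applying the text literally may declare non-inferiority or superiority confirmed on any of these contrasts.

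The trial could therefore miss its primary test at 1 month and still report confirmed non-inferiority for maintenance at 6 months, or for self-efficacy at 3 months, without departing from the Protocol. The Conclusions section makes adopting remote education as the preferred mode conditional on the hypothesis being confirmed, and does not say which contrast must carry it.

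**Working it through.** **Step 1. Reproduce the stated error rate.** The lower limit of a two-sided 95% CI gives a one-sided test at (1 − 0.95)/2 = 0.025. This equals the stated 2.5% for one test, so the primary contrast is controlled as intended. The sample size does not enter the error rates below.

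**Step 2. Count the contrasts the rule can reach.** Scales with a margin: maintenance, monitoring, management, self-efficacy = 4. Follow-ups: 1, 3 and 6 months = 3. Contrasts: 4 × 3 = 12. Non-primary: 12 − 1 = 11. Stoma QoL, PHQ-9 and OAI-23 have no margin. The non-inferiority rule cannot run on them, nor can the superiority rule, which also refers to the margin. They are outside the count.

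**Step 3. One analysis set.** Put every true effect at the margin and test each contrast at one-sided 0.025 (critical value 1.96). The chance of at least one false claim among k contrasts with common correlation ρ is

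1 − P(Z₁ < 1.96, …, Z_k < 1.96).

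For ρ = 0 this is 1 − 0.975^k; for ρ > 0 it was integrated numerically. The Protocol gives no correlations, so ρ is an assumption and a range is shown.

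| k = 11 | ρ = 0 | ρ = 0.5 | ρ = 0.8 |
|---|---|---|---|
| At least one false claim | 24.3% | 15.2% | 9.0% |
| Multiple of 2.5% | 9.7 | 6.1 | 3.6 |

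**Step 4. Both analysis sets, as the Protocol requires for non-inferiority.** Simulation with 400,000 runs: 4 scales × 3 visits, correlation between two contrasts = scale correlation × visit correlation, and a claim counted only if the ITT and per-protocol statistics both exceed 1.96. The correlation between the two sets is also assumed.

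| Scale / visit correlation | 11 contrasts, ITT–PP correlation 0.95 |
|---|---|
| 0.3 / 0.5 | 14.4% |
| 0.5 / 0.5 | 12.9% |
| 0.5 / 0.7 | 11.5% |
| 0.7 / 0.8 | 8.8% |

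With ITT–PP correlation 0.90 the range over the same settings is 12.5% down to 7.6%. Overall: 7.6% to 14.4%, or 7.6/2.5 = 3.0 to 14.4/2.5 = 5.8 times 2.5%.

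**Step 5. Superiority.** With all true effects at zero, the same 11 contrasts are each tested at one-sided 0.025, so the one-set range of Step 3 applies. It is not added to the non-inferiority range. If the truth is zero, a non-inferiority claim is correct. If the truth is at the margin (0.25 SD), then with 183 per arm the margin lies 0.25 × √(183/2) = 2.39 standard errors below zero. A false superiority claim would then need z of about 1.96 + 2.39 = 4.35, a probability of about 7 in a million per contrast.

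**The case against.** The strongest reply is that the handling of secondary endpoints is commonly left to the SAP, which is not at hand, so silence on multiplicity is no defect. As far as silence goes, that is right. The point here rests on what the Protocol does state: a confirmation rule without a stated scope. An SAP that restricted it would be narrowing the Protocol's own wording.

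A second reply is that the rules are phrased in the singular (one hypothesis, one margin), that the t-test sentence speaks of investigating differences, and that one outcome at one time is named as primary and the rest as secondary. This shows that a narrower reading is possible, and it shows that the primary is properly identified. It does not settle the scope, because the secondary OSCI scales have both a stated non-inferiority margin and, for monitoring and management, a stated objective.

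Several stronger readings are tempting and are not supported:

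- **The trial's 2.5% is broken.** It is not. The Protocol states 2.5% for the primary outcome, and that test keeps it.
- **The rule covers every secondary outcome.** Only the four OSCI scales have a margin, so larger counts that include quality of life, depression and adjustment describe tests the rule cannot perform.
- **The inflation is about six times.** That figure belongs to a single assumed correlation (0.5) on one analysis set. Under the two-set rule every scenario tried lies below it.
- **There are 24 tests.** Superiority is nested in non-inferiority on the same CI, and the two error sets do not add.

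Finally, all these rates put every scale at every visit exactly at the null boundary. That is the configuration against which error control is judged, not a forecast of what will happen.

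**Conclusion.** The point holds as a badly fixed decision rule. The wording lets non-inferiority or superiority be confirmed on 11 contrasts besides the primary, with no dependence on the primary's result. For false non-inferiority among those 11, the chance of at least one is about 8–14% under the Protocol's two-set requirement and about 9–24% on one set. For false superiority, where no two-set requirement is stated, it is about 9–24%. The multiple of 2.5% is roughly 3 to 10.

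These figures assume one-sided 2.5% per contrast, effects at the boundary, and correlations of 0 to 0.8 between contrasts and 0.90 to 0.95 between analysis sets, none of which the Protocol gives. The direction does not depend on them: every scenario tried is at least 3 times 2.5%. The matter affects how secondary and later-visit results may be worded. It does not touch the validity of the primary test. It should be corrected.

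**What to change.** In Planned statistical analyses, state that:

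1. The trial's non-inferiority conclusion rests only on self-care maintenance at 1 month, in both the ITT and per-protocol analyses.
2. Once that holds, superiority on the same contrast may be claimed from the same CI; no further gate is needed.
3. Any confirmatory claim on the secondary OSCI scales at 1 month is made only after success on the primary, either in a prespecified order that stops at the first failure or with an alpha split. The order is the sponsor's choice and should say where self-efficacy stands, since it has a margin.
4. All 3- and 6-month comparisons and all other outcomes are reported with 95% CIs as supportive or exploratory, without confirmatory wording.

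The cost is a few sentences, with no extra patients, visits or data, and the primary test keeps its full 2.5%. The real downside is that later-visit results and the results under objective 2 can no longer be worded as confirmed. The wording of objective 2 should be brought into line with that.

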Primary outcome. The primary outcome of this trial is self-care maintenance, assessed with the Ostomy Self-Care Index (OSCI) 12 Self-Care Maintenance Scale at 1 month after completion of the educational intervention performed by the ostomaterapists. The OSCI has 32 items grouped into four sections with 5-point Likert scale responses that assess the dimensions of self-care maintenance, self-care monitoring, self-care management and self-care efficacy. The section of self-care maintenance consists of nine items designed to assess daily behaviours for maintaining the physiological stability of the ostomy and peristomal skin (e.g., cleaning the ostomy and properly changing the collection device, following a diet according to the information received). The self-care maintenance section scores range from 0 to 100 where higher scores indicate better self-care behaviours. Self-care maintenance will be assessed at baseline (i.e., 15 days after discharge) in both the experimental and control groups. It will then be assessed at each follow-up (3 and 6 months after the end of the intervention) in both the experimental and control groups (Table 2).

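### The protocol names an unadjusted t test and a mixed model for the primary outcome without saying which 95% CI decides non-inferiority, and the t test leaves baseline score, stratification factors and centre unused

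*Protocol*

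**What the plan says.** All of this is in the protocol's METHODS.

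- **Test.** Planned statistical analyses states, for the primary and secondary non-inferiority outcomes, that "the student's t test for independent samples will be employed at each follow-up and baseline". No covariate is named.
- **Second analysis.** The next sentence reads: "A longitudinal linear mixed model will be implemented to analyze the effect of interventions on randomization groups and their interaction with time". It names no baseline score, stratification factor or centre. The reason given for this model is that it avoids losing subjects with missing data.
- **Decision rule.** Non-inferiority "will be confirmed if the lower extreme of the 95% confidence interval is not below the predetermined non-inferiority margin". The source of the interval is not given. Both the intention-to-treat and the per-protocol analysis must succeed.
- **Data available.** Under Primary outcome: "Self-care maintenance will be assessed at baseline (i.e., 15 days after discharge) in both the experimental and control groups". Under Randomization and blinding, allocation is by "randomisation stratified by type and sex of ostomy" (read here as ostomy type and patient's sex), and the blocks are distributed to the six centres.
- **Missing data.** Besides the mixed model's rationale, the text says that "the distributions of patients lost to follow-up between the two randomisation groups will be compared (using chi-square tests") and that results will be read in the light of any differences. No imputation is described.

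**The concern.** The 1-month effect can be estimated in two ways under this text, and one unassigned interval decides the trial. If the two intervals fall on different sides of -4, the protocol does not settle the result, and a choice made after seeing the data would raise the error rate.

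The t test is also the less efficient candidate. It uses neither the baseline value of the outcome nor the factors on which randomisation was balanced. If those factors are prognostic, its CI is wider than the design warrants.

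Finally, without imputation a t test at 1 month is an analysis of observed scores. The protocol expects 10% loss by then, and comparing the characteristics of those lost does not change the estimate.

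**Working it through.** **Inputs from the protocol.** Margin 4 points, planned "for a standardised non-inferiority margin equivalent to 0.25", so SD = 4 / 0.25 = 16 points. The alpha of 2.5% is read as one-sided, to match the lower limit of a 95% CI. Stated size: 183 evaluable per arm. Enrolled: 192 per arm; after the stated 10% loss, 192 × 0.9 = 172.8.

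**Assumptions.** True difference 0. The correlation r between baseline and 1-month scores is varied from 0.3 to 0.7 because the protocol gives none.

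**Stated sample size.** n per arm = 2 × ((1.96 + 0.842) / 0.25)² = 252 after rounding up. The stated 183 is not reproduced. That is a separate error under Sample size, but it means power starts low.

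**Precision and power.**

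- Half-width = 1.96 × 16 × √(2(1 − r²)/n)
- Power = Φ(0.25 / √(2(1 − r²)/n) − 1.96)

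Unadjusted at 183 per arm: half-width = 1.96 × 16 × √(2/183) = 3.28; power = Φ(2.391 − 1.96) = 66.7%.

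| r | Half-width, 183 per arm | Power, 183 per arm | Power, 172.8 per arm |
|---|---|---|---|
| unadjusted | 3.28 | 66.7% | 64.2% |
| 0.3 | 3.13 | 70.8% | 68.3% |
| 0.5 | 2.84 | 78.9% | 76.5% |
| 0.6 | 2.62 | 84.8% | 82.8% |
| 0.7 | 2.34 | 91.8% | 90.2% |

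A noncentral-t calculation agrees to within 0.3 percentage points.

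**Share of the gap to 80% recovered.** At 172.8 per arm the gap is 80 − 64.2 = 15.8 points. Adjustment recovers (68.3 − 64.2)/15.8 = 26% of it at r = 0.3, and 78% at r = 0.5. More than half is recovered only if r exceeds about 0.41, and 80% power needs r of about 0.56. At 183 per arm these thresholds are about 0.38 and 0.52.

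**Cost of the ambiguity.** Suppose the second analysis is baseline-adjusted. On the same patients the two estimates have correlation √(1 − r²), so joint probabilities follow from the bivariate normal distribution. At 172.8 per arm and true difference 0, the two intervals give opposite verdicts in roughly 10%, 18% and 23% of trials at r = 0.3, 0.5 and 0.6. At a true difference of -4, accepting whichever passes raises the one-sided error from 2.5% to 3.2%, 3.7% and 3.9%.

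**Missing scores.** With 10% of an arm missing, lowering the missing scores by d points moves that arm's mean by 0.10 × d. A 4-point shift moves it 0.4 points; a 10-point shift moves it 1 point, a quarter of the margin. Both values of d are illustrative.

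**The case against.** An unadjusted t test in a randomised trial is valid. Leaving out prognostic stratification factors makes its CI conservative, so a reader who infers that it inflates false claims of non-inferiority goes further than the text allows. Covariates for the mixed model and details of imputation often sit in a SAP, which is not at hand, and the protocol does not exclude covariates from that model. This stands, and it limits the efficiency point to an improvement. It does not answer the ambiguity: the protocol itself names the t test for these outcomes and leaves the deciding CI unassigned.

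A reader might also infer that missing data are handled only by the chi-square comparisons. The documents do not support that, since the mixed model is justified as a way to keep subjects with missing data. The completers-only description is a fair inference for the t test alone. If the model takes baseline as a time point, as Table 2 would allow, it already uses some baseline information; the text does not say.

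The low power comes from the Sample size paragraph: at 252 per arm the unadjusted t test would have the planned 80%. This also stands. Adjustment reduces the shortfall without removing its cause.

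**Conclusion.** The point holds as a recommended change. It is certain from the text that two analyses stand side by side, that the deciding CI is not identified, and that the t test uses none of the baseline score, stratification factors or centre.

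The size of the gain is conditional. With SD 16, no true difference and 10% loss, power rises from 64% to between 68% and 90% for r from 0.3 to 0.7. It is tempting to conclude that adjustment would recover most of the missing power. The documents do not support that without a condition: no correlation is given, baseline is taken at day 15 before four teaching sessions, and the outcome comes about a month after the day-60 session. At r = 0.3 only about a quarter of the gap is recovered. Any further gain from ostomy type, sex and centre cannot be quantified from the protocol.

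The figures for conflicting verdicts assume that the second analysis is baseline-adjusted. If it used no baseline information, differences between the two would come mainly from missing data.

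**What to change.** 1. Name one decisive analysis: the 1-month between-arm contrast from the planned mixed model, adjusted for baseline self-care maintenance, ostomy type, sex and centre. State that the lower limit of its 95% CI (remote minus in-person) is compared with -4 in both the intention-to-treat and per-protocol sets.
2. Make the follow-up t tests supportive only, and drop the t test of the outcome at baseline.
3. Keep all randomised patients in the intention-to-treat analysis. One month is the first follow-up, so patients lost for good before it have no follow-up score, and a model with baseline only as a covariate would omit them. Either treat baseline as an outcome visit with the arms constrained equal (in place of the baseline covariate), or use multiple imputation.
4. Any missing-data sensitivity analysis should shift imputed remote-arm values downward until the conclusion changes and report that point. It should not stop at 4 points, which moves the mean by only 0.4 when 10% are missing.
5. Give the expected gain as a range over r, and correct the sample size separately.

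The cost is protocol and SAP wording and slightly more analysis work. All covariates are already recorded, so there is no extra data collection.
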